### Ethical review

The study protocol was approved by the Ethics Committee of the Philosophical Faculty of the University of Zurich, Switzerland (date of approval: 13^th^ August, 2014). The trial will be conducted in compliance with the Helsinki Declaration.

### Randomisation and allocation concealment

To avoid spill over effects within each class, a cluster-randomised controlled trial will be conducted using school classes as a randomisation unit. Due to the heterogeneity of students in various disciplines (e.g. gender or professions), we will use separate randomisation lists for each school (stratified randomisation). Furthermore, to approximate equality of sample sizes in the study groups, we will use block randomisation with computer generated randomly permuted blocks of four cases [17].

The study assistants supervising the baseline assessment in vocational schools will not be informed about group allocation of classes. Group allocation will not be revealed to study participants until they provide informed consent, their username, mobile phone number, and baseline data. Furthermore, the interviewers conducting the computer assisted telephone interviews at the 6-months follow-up will be blinded when assessing the primary and secondary outcome measures.

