### Sample size calculation

The effect size estimation was based on the results of a randomized controlled trial testing the efficacy of *SMS-COACH* for smoking cessation among vocational school students that yielded a 7-day point prevalence rate of approximately 12% at the 6-month follow-up in the intervention group [8], and a pilot study testing the efficacy of an integrated smoking cessation and binge drinking intervention that yielded nearly a 1.5-fold increased smoking abstinence rate compared to a standard treatment control [15]. Based on these data, we assumed a 7-day point prevalence abstinence rate of 12% in the smoking cessation only group and 18% in the integrated intervention group at the 6-month follow-up. A sample size of n = 588 in each study group would have 80% power for a Chi-Square Test (α =5%, 2-sided) in order to detect this difference based on G-Power [18]. As vocational school students are nested within school classes, we needed to consider a potential design effect of 1.15 (assumed number of participants per school class: n = 4; intra-cluster correlation coefficient: 0.05 [8]), resulting in an estimated required sample size of n = 675 per study group and a total of N = 1350 study participants.

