### Data analyses

We will use regression models to compare the efficacy of the interventions on the different outcome measures. If necessary, we will control for baseline differences by entering additional baseline variables as covariates to the regression models. All analyses will be performed considering the intention-to-treat principle. Given the clustered nature of the data (students in different classes), we will compute robust variance estimators for all regression analyses.

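### Randomisation is stratified by school, but the stated analysis rule does not bring school into the models; if schools differ in outcome, the standard errors are mildly conservative

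*Protocol article*

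**What the plan says.** Under Randomisation and allocation concealment, the protocol article allocates "using school classes as a randomisation unit" and says "we will use separate randomisation lists for each school (stratified randomisation". The reason it gives is "Due to the heterogeneity of students in various disciplines (e.g. gender or professions". Allocation within each list uses "computer generated randomly permuted blocks of four cases".

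The Data analyses section plans regression models for all outcomes under intention to treat. It makes two statements about structure and adjustment. On structure: "Given the clustered nature of the data (students in different classes), we will compute robust variance estimators for all regression analyses". On adjustment: "If necessary, we will control for baseline differences by entering additional baseline variables as covariates to the regression models". School is not named in that section, and nothing there says that it will be left out.

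The Sample size calculation section assumes "12% in the smoking cessation only group and 18% in the integrated intervention group", then applies a design effect of 1.15 based on 4 participants per class and an intra-cluster correlation of 0.05. It counts on no gain from stratification.

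**The concern.** The design treats school as important enough to stratify on, and the analysis should follow the design. When arms are balanced within schools, differences between schools cancel out of the treatment contrast. A variance that is clustered on class but has no school term still counts those differences as error, so the reported standard error exceeds the true sampling variability of the estimate.

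The adjustment rule does not repair this. It responds to baseline differences between the arms, and stratified blocks are meant to prevent such differences for school. The variable that the design singles out is therefore among the least likely to meet the condition. The rule also leaves the decision on school until the baseline data have been seen.

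At stake are intervals somewhat wider than needed and a little lost power, for a comparison of two active programmes whose expected difference is only 6 percentage points.

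**Working it through.** **Inputs from the protocol article (Sample size calculation).** Abstinence 12% and 18%; two-sided 5%; 588 per arm before clustering; 4 participants per class; intra-cluster correlation 0.05; design effect 1.15; 675 per arm, 1350 in total.

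**Reproducing the plan's figures.** The two-proportion formula with continuity correction gives 588 per arm, an exact match. Without the correction (pooled variance) it gives 555. The design effect is 1 + (4 − 1) × 0.05 = 1.15, and 588 × 1.15 = 676.2 against the stated 675, which is a rounding difference. At 675 per arm the effective size is 675/1.15 = 587, where the uncorrected chi-square test has 82.2% power. That is the baseline used below.

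**Assumption.** The documents do not divide the 0.05 into between-school and within-school parts. Let s be the between-school part, from 0 to 0.05, with arms fully balanced within schools.

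**Formulas.**
- Variance inflation seen by class-robust standard errors without school: 0.95 + 4 × 0.05 = 1.15.
- True variance inflation of the contrast: D = 0.95 + 4 × (0.05 − s) = 1.15 − 4s.
- Overstatement of the standard error: R = √(1.15/D).
- True two-sided error without school: 2 × [1 − Φ(1.96 R)].
- Power without school: Φ[(0.06 − 1.96 √(1.15 V0)) / √(D V1)]. Power with school: the same, with D in place of 1.15. Here V0 = 2 × 0.15 × 0.85/675 and V1 = (0.12 × 0.88 + 0.18 × 0.82)/675.

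**Example, s = 0.02.** D = 1.15 − 0.08 = 1.07. The variance ratio is 1.15/1.07 = 1.075, R = 1.037, and the true error is 4.2%.

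| s | D | SE overstated by | True error without school | Power without school | Power with school |
|---|---|---|---|---|---|
| 0 | 1.15 | 0% | 5.0% | 82.2% | 82.2% |
| 0.01 | 1.11 | 1.8% | 4.6% | 82.6% | 83.5% |
| 0.02 | 1.07 | 3.7% | 4.2% | 83.0% | 84.8% |
| 0.025 | 1.05 | 4.7% | 4.0% | 83.3% | 85.5% |
| 0.04 | 0.99 | 7.8% | 3.5% | 84.0% | 87.4% |
| 0.05 | 0.95 | 10.0% | 3.1% | 84.5% | 88.7% |

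The last row is a ceiling: all of the correlation within classes would have to come from schools. There the variance ratio is 1.15/0.95 = 1.211, and the power forgone is 88.7 − 84.5 = 4.2 points.

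**Simulation check.** Linear probability model, blocks of four classes within school, about 338 classes (1350/4 = 337.5), 1500 runs per setting. Simulation error is about 1 point on power and 0.6 points on type I error.
- With 12 classes per school and s = 0.025 under no effect, the estimate had an empirical standard deviation of 0.0200 both with and without school terms. The mean reported standard error was 0.0208 without school and 0.0199 with it. The estimate keeps the stratification gain; only the reported standard error misses it.
- With 12 classes per school and s = 0.04, power was 82.9% without school and 86.9% with it.
- With 3 classes per school, school fixed effects lowered power: from 82.4% to 77.9% at s = 0, and from 83.3% to 78.9% at s = 0.01.
- With school fixed effects and 12, 6 or 3 classes per school, rejection under no effect ran from 4.7% to 6.1%.

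**The case against.** The strongest reply is that a condensed article need not list model terms. The Data analyses section names no covariates, link function or strata, and an analysis plan that is not shown may well include school. That stands against any claim that the trial has decided to ignore school. It does not dispose of the point, because the article does state a rule for what enters the models, and that rule depends on observed imbalance.

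Second, the harm needs schools to differ in abstinence or consumption. The stated reason for stratifying concerns the make-up of the student body, not the outcome, and no between-school variance is given. This stands, so the size can only be shown as a range that starts at zero. The range also assumes full balance within schools; a school whose number of classes leaves a block incomplete would show a smaller effect.

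Third, adding school is not free. The documents give neither the number of schools nor the classes per school, and the simulation shows a loss of about 4 points when schools are small and alike. Under logistic regression there is also sparseness: a school with 3 classes of 4 has 12 students, and at 15% abstinence (the mean of 12% and 18%) the chance of no quitters is 0.85^12 = 14%, taking students as independent. The odds ratio would also become conditional on school. This stands and shapes the fix.

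A reader might infer that the precision gained by stratifying is thrown away, or that the planned p-values are invalid. The documents support neither. The estimate itself keeps the gain, any error is in the conservative direction, and the sample size does not rely on stratification.

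**Conclusion.** The point holds as a minor one. The stated analysis does not by itself bring the stratification factor into the models, and if schools differ in outcome, class-robust standard errors without school are conservative. For the abstinence outcome the overstatement is 0% to about 10%, and about 2% to 5% if 0.01 to 0.025 of the correlation lies between schools. The true error stays between 3.1% and 5.0%. Power without school is 82% to 85%, above the planned 80%, and the power forgone is 0 to about 4 points.

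These figures rest on the protocol's 4 participants per class and intra-cluster correlation of 0.05, an assumed between-school share, and balance within schools. No corresponding figures are given for cigarette consumption, the other primary outcome; the direction is the same but the size cannot be stated.

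**What to change.** State in the Data analyses section, before outcome data are seen, that school enters the primary and secondary regression models as the stratification factor regardless of observed baseline differences, with robust variances still clustered on class.

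Add a rule for small schools in the same place: either pool schools that contribute few classes, or classes in only one arm, into predefined larger strata, or fit school as a random intercept. The threshold for pooling can be set from the list of participating schools without sight of outcomes. For a logistic model, say also that the odds ratio is conditional on school.

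The cost is two or three sentences and one predefined threshold. No change to randomisation, sample size or data collection is needed. The small-school rule is an essential part of the change, since unpooled fixed effects for many small schools could cost as much power as the adjustment recovers.

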### Sample size calculation

The effect size estimation was based on the results of a randomized controlled trial testing the efficacy of *SMS-COACH* for smoking cessation among vocational school students that yielded a 7-day point prevalence rate of approximately 12% at the 6-month follow-up in the intervention group [8], and a pilot study testing the efficacy of an integrated smoking cessation and binge drinking intervention that yielded nearly a 1.5-fold increased smoking abstinence rate compared to a standard treatment control [15]. Based on these data, we assumed a 7-day point prevalence abstinence rate of 12% in the smoking cessation only group and 18% in the integrated intervention group at the 6-month follow-up. A sample size of n = 588 in each study group would have 80% power for a Chi-Square Test (α =5%, 2-sided) in order to detect this difference based on G-Power [18]. As vocational school students are nested within school classes, we needed to consider a potential design effect of 1.15 (assumed number of participants per school class: n = 4; intra-cluster correlation coefficient: 0.05 [8]), resulting in an estimated required sample size of n = 675 per study group and a total of N = 1350 study participants.

### Intervention

#### Technological background

The *MCT* and the *MCT +* were developed using the *MobileCoach* system. This modular, web-based system allows an author to easily describe and optimize all parts of an intervention: baseline assessment survey, tailored web-based feedback, intervention rules, text messages with combined content according to group and media, as well as the interplay between these. When using the web-based application interface, technical programming skills are not required for these processes. The open source code of the *MobileCoach* system will be made available on http://mobile-coach.eu by the end of 2014. Two particular aspects of the technical implementation will be discussed here; for further details of the *MobileCoach*, see [19].

The participant–*MobileCoach* system interface is based on SMS text messages. To overcome privacy issues on social networks and the internet in general, SMS offers three advantages: (1) it is safer than typical internet-based technologies (e.g., email, Facebook) because the communication is controlled by one negotiating agent, the mobile operators; (2) the unique phone number allows the system to unambiguously identify each participant by an incoming message, and (3) there is no need for an additional, platform-specific mobile phone application or account. In combination with unique URLs to access audio-visual media content sent with specific text messages, the system can also determine if the content has been viewed by a particular participant.

Another interesting aspect of the *MobileCoach* implementation is the rule-based problem solving approach that builds on the foundations of automata theory [20], rather than the traditional procedural approach. Thus, the system can handle very complex interrelationships involving several variables. Triggered by a small number of possible events (e.g., the participant answers/does not answer a specific text message within a specific time frame) or triggered at a specific time, the system tailors the subsequent intervention steps to the specific user at any time. To do this, the intervention rule-set is applied to the present values of the participants that represent their latest health and behavioural status. With this approach, individually tailored interventions can be modelled with a simple set of rules.

#### Theoretical background

The smoking cessation intervention is primarily based on the HAPA [10]. This health behaviour model suggests a distinction between motivation processes resulting in goal setting (individuals in this stage are called ‘pre-intenders’) and volition processes leading to the actual health behaviour (subdivided into inactive individuals, ‘intenders’; and those who have already adopted these health behaviour, ‘actors’).

Outcome expectancies (pros of smoking cessation and cons of further smoking), risk perception, and perceived self-efficacy in the initial pre-intentional stage are seen as important social-cognitive predictors that promote the intention to act. In the subsequent intentional stage, planning processes are crucial to achieve the desired action. Once an action has been initiated, self-regulatory skills are important to help maintain the health behaviour, e.g. how to cope with craving situations. Additionally, we integrated elements derived from the Social Norms Approach [21] and implementation intentions, ‘if-then’ plans that link situational cues with responses that are effective in attaining a desired outcome [22], into the present intervention.

The alcohol intervention provides normative feedback based on the social norms approach [21], which constitutes the theoretical background of the majority of evidence-based internet interventions to reduce problem drinking in young people [23, 24].

#### Overview of intervention components

After participating in the baseline survey, participants assigned to the *MCT+*, the combined web- and text messaging-based integrated smoking cessation and alcohol intervention will (1) receive individually tailored web-based feedback on their drinking behaviour compared to a reference group representing age and gender norms, (2) receive individually tailored text messages via mobile phones to promote low-risk drinking behaviour for 3-month period, (3) receive individually tailored mobile phone text messages to support smoking cessation for a 3-month period, and (4) be offered the possibility to register for a more intensive program providing strategies for smoking cessation centred around a self-defined quit date.

Participants assigned to *MCT,* the smoking cessation-only intervention, will (1) receive individually tailored mobile phone text messages to support smoking cessation for a 3-month period, and (2) be offered the possibility to register for a more intensive program providing strategies for smoking cessation centred around a self-defined quit date.

The text messages will typically be 150–200 characters long, some of which will include web links to thematically appropriate video clips, pictures, and websites.

#### Web-based feedback on drinking behaviour (MCT+)

Web-based feedback will be provided for participants receiving the *MCT +* immediately after completion of their baseline assessment. The content is based on effective intervention programs developed primarily for college and university students in the USA and Canada [25, 26] modified for the target group of German-speaking adolescents in Switzerland aged 16–20 with varied educational backgrounds. Age- and gender-specific norms for alcohol consumption were derived from a previous study [27] which assessed frequency of risky single occasion drinking, alcohol volume, and the maximum number of drinks consumed on a single occasion among 973 vocational and upper secondary school students in the Canton of Zurich, Switzerland. The web-based feedback includes individually tailored graphical and textual information concerning (1) the number of drinks consumed per week in relation to age and gender-specific reference groups (2) expenditure on drinking, (3) calorific value of consumed alcoholic drinks, and (4) frequency of risky single-occasion drinking in relation to age- and gender-specific reference groups.

#### Text messages stimulating drinking within low-risk limits (MCT+)

Only participants of the *MCT +* group who reported risky single-occasion drinking at the baseline—defined as consuming 5 or more drinks on an occasion for men and 4 or more drinks for women within the previous month—will receive one weekly text message promoting drinking within low-risk limits for a 3 month-period. Every alternative week, this text message will be sent on Saturdays at 7 pm, and during the other weeks, it will be sent on individual’s typical drinking day and time (e.g. Friday at 10 pm).

The text messages will provide information on (1) strategies for drinking within low-risk limits, and (2) the association between smoking and alcohol consumption, particularly on the importance of avoiding alcohol or consuming minimal amounts in order to successfully achieve smoking abstinence for those participants who intend to quit smoking or have already quit. E.g., ‘Hey Susan! Studies show that alcohol consumption clearly leads to an increased desire to smoke. Remember this when you go out the next time and try drinking little or even no alcohol at all. It will be easier for you not to smoke’.

#### Text messages to support smoking cessation (MCT + and MCT)

During the 3-month intervention period, participants in both intervention groups will receive one text message prompt per week that either assesses smoking-related target behaviours or encourages participation in a quiz or a message contest. These prompts can be answered easily by typing a single letter, number, or a sentence using the mobile phone’s reply function. The weekly SMS prompt will be sent at a fixed time each week (Tuesday at 6 pm). The content of the prompt will depend on the individual HAPA stage as well as the number of the intervention week (odd or even).

Smoking-related target behaviour includes the HAPA stage, assessed every 4 weeks by responses to the question: ‘Have you recently smoked cigarettes?’, with the following response options (1) ‘Yes, and I do not intend to quit’ (pre-intender), (2) ‘Yes, but I am considering quitting’ (pre-intender), (3) ‘Yes, but I seriously intend to quit’ (intender), or (4) ‘No, I quit smoking’ (actor). Furthermore, among pre-intenders, we assess the number of cigarettes smoked per day or week (depending on smoking status: daily/occasionally), every 4 weeks, while for intenders and actors, we assess whether the individually chosen strategies to cope with craving situations, assessed within the baseline assessment, were applied, e.g. ‘Did you apply the following strategy recently? When I am at a party, I distract myself from smoking by dancing. Yes (Y) No (N)’.

Participants will receive an immediate feedback SMS after their response on the prompts regarding smoking-related target behaviours, e.g. ‘You can be really proud of yourself! Since the last assessment, you’ve smoked about 4 cigarettes less per day. That means you’re on the right path towards an active and healthy lifestyle.’

Furthermore, 48 hours after this prompt (Thursday at 6 pm) they will receive an additional message tailored to the current HAPA stage and individual data provided at the baseline assessment. Pre-intenders will receive text messages providing information (1) on the risks of smoking, (2) on the benefits of smoking cessation, and (3) regarding methods to improve self-efficacy for smoking cessation. Intenders and actors will receive text messages providing information (1) on how to use individual resources for quitting (e.g. social support), (2) on how to overcome barriers to smoking cessation (e.g. friends who smoke and stress), and (3) methods to improve self-efficacy for smoking cessation. Sample text messages for the different stages and content categories are displayed in Table 1.

**Table 1 Tab1:** **Sample text messages**

Stage of smoking cessation	Content category	Exemplary text message
Pre-Intention	Risks of smoking	Hi Mary. Smoking and birth control pills aren’t suited to each other. If you smoke while on hormonal birth control, your blood vessels are likely to become constricted and can get blocked. Even for young women, the risk of a heart attack or stroke increases significantly.
	Benefits of smoking cessation	Hi Mike. Even though you aren’t quite convinced yet, we think you should consider quitting; without the constant urge to smoke and buy cigarettes, you’ll feel more independent and confident. Have a look at this video: https://f.mobile-coach.eu/147
	Self-efficacy for smoking cessation	Hi Lizzy. Have you ever wanted to do something that is difficult, such as doing very well at work or similar? Did you succeed? These experiences may also help you become smoke-free!
Intention	Smoking cessation resources	Hi Peter. Sports and exercise can make becoming smoke-free a lot easier. They distract you and result in elevated mood. Maybe you could regularly meet up with a friend to go running, ride bikes, or for other sports activities.
	Barriers to smoking cessation	Hi Alex. Do you have a strong urge to smoke? So does Julia. Both of you are in the same situation. Maybe you could find distractions by spending time together: http://www.juliarauchfrei.at
Action	Self-efficacy for smoking cessation	There are forums online in which smokers and ex-smokers exchange their experiences on smoking cessation. Have a look at http://www.stop-dependance.ch/tabak/forum/

A quiz will be conducted thrice during the intervention period and will include questions concerning: (1) smoking norms (percentage of smokers within the age- and gender-specific reference groups), (2) health consequences of smoking cessation (days until positive health consequences after smoking cessation), and (3) expenditure on cigarettes (money spent for cigarettes per year). Participants will receive immediate individualized feedback on their answer. If they do not respond within 48 hours, they will be sent the correct response.

A contest that requires participants to create a text message to motivate other participants to quit smoking (for intenders) or provide concrete ways to help others quit smoking (for intenders and actors) will be conducted twice during the intervention period. The best text message from each of the two categories, rated weekly by a tobacco cessation expert from the Swiss Research Institute for Public Health and Addiction, will be sent anonymously to participants in the respective category after 48 hours.

